### Follow‐up

2.6

After randomization, the following data are being collected in each group: number of RBC units, type of RBC (autologous or homologous), duration of RBC conservation, and associated transfusion of non‐RBC blood products (platelets, coagulation factors, etc.). The collection of outcome data is being performed by the investigator at discharge or 30 days, whichever occurs first. After discharge, patient follow‐up is scheduled at Day 30 (±5 days) and follow‐up data are collected by the investigator, either by direct contact (if the patient is still hospitalized) or by a visit, phone call, or mail. The EQ‐5D HRQoL questionnaire is completed by the patients.

At 6 months (±30 days) and 1 year (±30 days), patients are contacted to collect clinical event and HRQoL (EQ‐5D questionnaire) data.

### Statistical methods

2.7

#### Power and sample size considerations

2.7.1

There is no established clinical superiority of either transfusion strategy at this stage. We hypothesized that a restrictive transfusion strategy would be clinically noninferior to a liberal transfusion strategy but less costly. As our hypotheses are clinical noninferiority but superior cost‐effectiveness of the restrictive transfusion strategy, we based our power calculations on clinical grounds. We anticipated MACE rates of 11% in the restrictive transfusion strategy and 15% in the liberal transfusion strategy, based on observations from the nationwide French registry of acute ST‐Elevation or non‐ST‐elevation myocardial infarction (FAST‐MI) program.^25^ Based on these hypotheses, a sample size of 300 patients per group would provide 80% power to demonstrate noninferiority of the restrictive group, with a noninferiority margin corresponding to a relative risk equal to 1.25, using a confidence interval (CI) method with a 97.5% one‐sided CI. With a conservative hypothesis of 5% of patients with major protocol violations, a total of 630 patients (315 in each arm) are required for the trial to be adequately powered for both intention‐to‐treat (ITT) and per‐protocol (PP) analyses. Using the formula for sample size calculation in economic evaluation, we estimated that this sample size would allow us to show cost‐effectiveness at a threshold of €50 000, a power of 80%, and a significance level of 5%, a €1000 difference in costs and 0.15 difference in QALYs.^26^
$$n=\frac{2\;{\left(z_{\propto }+z_{\beta }\right)}^{2}\left({\mathrm{sd}}_{c}^{2}+{\left(\mathrm{Ws}d_{q}\right)}^{2}-\left(2\mathrm{W\rho s}d_{c}sd_{q}\right)\right)}{{\left(W∆Q-∆C\right)}^{2}}.$$where *C* and *Q* represent costs and utilities, *W* willingness to pay, and *ρ* the correlation between costs and quality of life (set at −0.1).

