**Results:**

The trial aimed to enroll 630 patients. Based on estimated event rates of 11% in the restrictive group and 15% in the liberal group, this number will provide 80% power to demonstrate clinical noninferiority of the restrictive group, with a noninferiority margin corresponding to a relative risk equal to 1.25. The sample size will also provide 80% power to show the cost‐effectiveness of the restrictive strategy at a threshold of €50 000 per quality‐adjusted life year.

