#### Primary clinical outcome analysis

2.7.5

Noninferiority will be considered to have been demonstrated if the upper value of the 97.5% one‐sided CI of the relative risk is inferior to the noninferiority margin equal to 1.25, in both the PP and ITT populations. If noninferiority of the restrictive strategy is established, sequential testing of superiority of the restrictive strategy will be accepted if the upper value of the 97.5% one‐sided CI of the relative risk is inferior to one.

All individual components of the primary outcome will be analyzed by Chi‐square or Fisher's exact tests. As these analyses will be exploratory, no adjustment of the alpha value for multiplicity will be made.

Times to death and MACE during 1‐year follow‐up will be described by Kaplan‐Meier curves and tested by log‐rank test. The reference date is defined as the randomization date. All patients will be censored at the time of the last observation.

All safety endpoints will be analyzed by Chi‐square or Fisher's exact tests.

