Clinical data regarding transfusions in AMI are mainly observational and yield inconsistent results. An analysis of the Controlled Abciximab and Device Investigation to Lower Late Angioplasty Complications (CADILLAC) trial found that transfusion was independently associated with 30‐day and 1‐year death, and concluded that transfusion may be harmful after primary percutaneous coronary intervention.^35^ Similarly, a pooled analysis of three international ACS trials found that blood transfusion was associated with higher death after adjustment for confounding factors.^36^ Conversely, a retrospective analysis of nearly 80 000 elderly patients hospitalized with AMI reported lower 30 day death in those with hematocrit <33% who received transfusions vs those who did not (adjusted odds ratio [OR] 0.69, 95% CI 0.53‐0.89).^5^ A meta‐analysis (>200 000 patients) reported a higher risk of death and recurrent myocardial infarction in patients with AMI who received transfusions (OR 2.91, 95% CI 2.46‐3.44).^6^ However, another meta‐analysis of observational studies in post‐ACS patients suggested that transfusion had a neutral or beneficial effect when undertaken at hemoglobin levels <8 g/dL, whereas it could be harmful at hemoglobin >11 g/dL. These apparently contradictory observations are likely related to the limitations of observational studies. The majority of patients undergoing blood transfusion cannot be matched with nontransfused patients due to their markedly different clinical profiles,^37^ indicating that observational studies cannot reliably establish the benefits or risks of transfusion because they are hopelessly influenced by selection bias. In addition, in an observational setting, it is difficult to unravel the effect of anemia, bleeding, and transfusion on outcomes.^1^ There may also be a differential effect of transfusion according to hemoglobin nadir or the presence of overt bleeding.^38^

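### The stated 80% power does not match the planned relative-risk test: with the article's own inputs, 300 patients per group give about 70%

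*Protocol article*

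**What the plan says.** The planning inputs are in section 2.7.1 (Power and sample size considerations) of the protocol article:

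- Event rates: "We anticipated MACE rates of 11% in the restrictive transfusion strategy and 15% in the liberal transfusion strategy".
- Margin: "with a noninferiority margin corresponding to a relative risk equal to 1.25".
- Level: "using a confidence interval (CI) method with a 97.5% one‐sided CI".
- Result: "a sample size of 300 patients per group would provide 80% power to demonstrate noninferiority of the restrictive group".

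The same section adds 5% for major protocol violations, reaches 315 per arm (630 in total), and concludes that this is enough for both the ITT and the PP analyses. The Abstract attaches the claim to the total of 630: "this number will provide 80% power to demonstrate clinical noninferiority of the restrictive group".

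Section 2.7.5 (Primary clinical outcome analysis) sets the decision rule. Noninferiority needs the upper limit of the one-sided 97.5% interval "of the relative risk is inferior to the noninferiority margin equal to 1.25, in both the PP and ITT populations".

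**The concern.** The rates, group size, margin, level and test statistic are all printed, so the power can be recomputed without borrowing any input. When this is done for the section 2.7.5 rule, the result is about ten points below the stated 80%.

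At stake is what readers are told about the primary clinical comparison. If the assumed rates are true, the chance of failing to show noninferiority is about 30% in the PP population, not 20%. The rule requires success in both populations, so the claim that 630 patients suffice for both at 80% does not hold under the article's own assumptions. Anyone interpreting an inconclusive result would start from an overstated view of the trial's sensitivity.

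**Working it through.** **Inputs** (sections 2.7.1 and 2.7.5): p_R = 0.11, p_L = 0.15, so the assumed relative risk is 0.11/0.15 = 0.733; margin 1.25; one-sided level 0.025 (z = 1.960); 300 per arm, or 315 per arm before the 5% allowance (315 × 0.95 ≈ 299).

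**1. Trying to reproduce 80% with the planned test.** On the log relative-risk scale:

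- Distance to the margin: ln 1.25 − ln 0.733 = 0.223 + 0.310 = 0.533.
- Standard error at 300 per arm: √[0.89/(300 × 0.11) + 0.85/(300 × 0.15)] = √(0.89/33 + 0.85/45) = 0.214.
- Power = Φ(0.5333/0.2142 − 1.960) = Φ(2.490 − 1.960) = Φ(0.530) = 70.2%.

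The 80% is not reproduced.

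**2. Does the choice of relative-risk method matter?** Very little:

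| Method (one-sided 0.025) | 300 per arm | 315 per arm |
|---|---|---|
| Log relative-risk formula | 70.2% | 72.3% |
| Exact binomial enumeration, log-Wald interval | 70.9% | 72.9% |
| Exact binomial enumeration, score test for the ratio | 71.0% | 73.0% |
| Linearised contrast p_R − 1.25 p_L | 69.2% | 71.3% |

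**3. Size needed for 80%.** n = (1.960 + 0.842)² × (0.89/0.11 + 0.85/0.15) / 0.5333² = 7.849 × 13.758 / 0.2844 ≈ 380 evaluable per arm. Allowing for 5% exclusions, 380/0.95 = 400 per arm, or about 800 in total against 630.

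**4. Passing in both populations.** Joint power cannot exceed power in the smaller PP set, about 70%. A simulation with 315 per arm in ITT and 299 in PP, with exclusions at random, gave 68.7%.

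**5. Calculations that do come close to 80% at 300 per arm:**

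- *Fixed risk-difference margin.* 0.25 × 15% = 3.75 points. Standard error = √[(0.11 × 0.89 + 0.15 × 0.85)/300] = 0.0274. Power = Φ[(0.0375 + 0.04)/0.0274 − 1.960] = Φ(0.867) = 80.7%; the size for 80% is 295 per arm.
- *Log relative risk at a one-sided 5% level.* Φ(2.490 − 1.645) = 80.1%; the size for 80% is exactly 300 per arm.
- *Risk-difference interval against 0.25 times the observed control rate.* By enumeration, 78.2% at 300 and 79.8% at 315.

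The first and third do not test the relative-risk interval. The second uses a level that contradicts the 97.5% interval in both sections.

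**The case against.** The strongest defence is that 300 is not arbitrary. Section 2.7.1 speaks of a margin that corresponds to a relative risk of 1.25 and of a confidence interval method. That wording leaves room for converting the margin to 3.75 points at the 15% reference rate, and 300 per arm then gives just over 80% at the stated level. This stands as a possible origin of the number, so the fault is best described as a mismatch between the power calculation and the planned analysis. It does not rescue the 80%, because section 2.7.5 decides on the relative-risk interval.

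It also stands that the decision rule, margin and type I error are untouched, that enrolment closed in October 2019, and that the declared primary endpoint is the 30-day ICER, with MACE noninferiority as the primary clinical outcome.

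A reader might infer more than the article supports:

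- *That 80% can arise by only one or two routes, or that the sponsor used a particular one.* At least three calculations land near 80%, and the article does not say which was used.
- *That planning on a benefit of the restrictive arm is itself an error.* The article says "There is no established clinical superiority of either transfusion strategy at this stage" and, in the Discussion, that "observational studies cannot reliably establish the benefits or risks of transfusion because they are hopelessly influenced by selection bias". Neither statement conflicts with an openly declared planning assumption taken from a registry; a noninferiority trial may be powered under an assumed benefit.
- *That the trial will most likely fail.* This holds only if the true rates are equal. Power at 300 per arm would then be 21%, 18% or 16% at common rates of 15%, 13% or 11%. The article never claims 80% for that scenario, and leaving it out is a planning and reporting choice.

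**Conclusion.** The point holds as a mismatch between the stated power and the planned test. For the section 2.7.5 rule, power is about 70-71% at 300 per arm and about 72-73% at 315 per arm (the linearised approximation is about one point lower at each size). The 80% in the Abstract and section 2.7.1 is therefore overstated by about ten points for PP and seven to eight for ITT, and joint power is capped at about 70%.

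These figures rest on the article's own rates of 11% and 15%, equal allocation and independent binomial outcomes. The joint figure of about 69% further assumes that the 5% of exclusions are random; the cap does not. The validity of the eventual noninferiority conclusion is not affected, only what the article says about the chance of reaching it.

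**What to change.** Keep the 1.25 margin, the one-sided 97.5% interval and the 630 patients. Then:

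1. In the Abstract and section 2.7.1, restate the power for the section 2.7.5 test as about 70% at 300 per arm (PP) and about 72-73% at 315 per arm (ITT).
2. Correct the statement that 630 patients give adequate power for both populations, and say that joint power cannot exceed the PP figure (about 69% with random exclusions).
3. If another calculation produced 300 per group, name its scale, margin and level, and say that it differs from the section 2.7.5 test.

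Reporting power under equal true rates (about 16-21%) beside these figures would be informative but is optional.

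The cost is wording only: no extra patients and no change to the analysis, but a less favourable power statement.

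### The 80% economic power assumes a 0.15 QALY gain; the planned 4-point MACE difference can supply at most about 0.04 QALY in one year, and no other source is stated

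*Protocol article*

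**What the plan says.** Section 2.7.1 of the protocol article (Power and sample size considerations) sets the sample size on clinical grounds: "We anticipated MACE rates of 11% in the restrictive transfusion strategy and 15% in the liberal transfusion strategy". After an allowance for protocol violations, "a total of 630 patients (315 in each arm) are required".

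The paragraph then turns to the economic evaluation. It states that this sample size would show cost-effectiveness at a threshold of €50 000, with "a power of 80%, and a significance level of 5"%, for a €1000 "difference in costs and 0.15 difference in QALYs". A net-benefit formula is printed, in which C and Q "represent costs and utilities" and ρ is "the correlation between costs and quality of life (set at" −0.1). The formula needs an SD of costs and an SD of QALYs, but the article gives values for neither. Nor does it give a sign for the €1000, the sidedness of the 5%, or a source for 0.15.

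The Abstract (Results) repeats the claim as a property of the design: "The sample size will also provide 80% power to show" cost-effectiveness at €50 000 per QALY. It does not mention 0.15.

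Table 2 and section 2.4 put QALYs at 1 year, and section 2.1 gives 1 year of participation per patient. The hypothesis, in the Abstract and section 2.7.1, is that the restrictive strategy is clinically noninferior and less costly.

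**The concern.** Two planning assumptions stand in one paragraph and do not fit together. One fixes the expected clinical benefit at 4 fewer MACE per 100 patients. The other fixes the expected health gain at 0.15 QALY per patient within a year. No one can lose more than about one QALY in a year, so few averted events cannot add up to a large average gain.

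This matters because 0.15 drives the economic power. In the printed formula the detectable net benefit is W·ΔQ − ΔC. At ΔQ = 0.15 the health term is 50 000 × 0.15 = €7500, against €1000 for costs. A much smaller QALY difference shrinks the effect to be detected, and the 80% no longer follows. A reader of the Abstract sees only the 80% and could take an inconclusive cost-utility result as coming from an analysis adequately powered under the trial's own assumptions.

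**Working it through.** **Inputs from the protocol article.** W = €50 000 per QALY; ΔQ = 0.15; |ΔC| = €1000; ρ = −0.1; power 80%; α = 5%; 315 per arm; MACE 11% versus 15%; QALY horizon 1 year. The restrictive strategy is hypothesized to be less costly, so I take ΔC = −1000.

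**Not in the article, hence assumed.** The SDs of cost and QALY, and the sidedness of the test (both tried).

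**Step 1: the QALY ceiling.** With death at 0 and full health at 1, a patient loses at most 1 QALY in a year.
- Planned difference: 0.15 − 0.11 = 0.04 events per patient.
- Largest gain through MACE: 0.04 × 1 = 0.04 QALY per patient. This needs every averted event to be a day-0 death in a patient otherwise in full health for the year. MACE also includes nonfatal stroke, nonfatal MI and emergency revascularization, so the realistic figure is lower.
- Loss per averted event needed to reach 0.15: 0.15 / 0.04 = 3.75 QALYs, which one year cannot hold.
- Remainder to be found outside MACE: 0.15 − 0.04 = 0.11 QALY per patient on average.

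**Step 2: can the stated 80% be reproduced?** The formula is n = 2(z_α + z_β)²·S² / (W·ΔQ − ΔC)², with S² = sd_c² + (W·sd_q)² − 2Wρ·sd_c·sd_q. Without the SDs it cannot be run forward, so the 80% can be neither confirmed nor refuted. It can be solved backward for S at n = 315, with W·ΔQ − ΔC = 7500 + 1000 = €8500:
- Two-sided: z_α + z_β = 1.960 + 0.842 = 2.802; S = 8500 × √(315/2) / 2.802 ≈ €38 100.
- One-sided: z_α + z_β = 1.645 + 0.842 = 2.486; S ≈ €42 900.

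**Step 3: power at the ceiling, same S.** With ΔQ = 0.04, net benefit is 2000 + 1000 = €3000. Only the ratio 3000/8500 = 0.353 matters, so the result does not depend on how S splits between cost and QALY.
- Two-sided: Φ(0.353 × 2.802 − 1.960) = Φ(−0.971) = 17%.
- One-sided: Φ(0.353 × 2.486 − 1.645) = Φ(−0.767) = 22%.
- n for 80%: 315 × (8500/3000)² ≈ 2529 per arm. This shows scale only and is not a proposal.

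**Step 4: power at the ceiling under assumed smaller SDs.** Two-sided, 315 per arm, power = Φ(3000 / (S·√(2/315)) − 1.960):

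| Assumed sd_q | Assumed sd_c (€) | S (€) | Power at ΔQ = 0.04 |
|---|---|---|---|
| 0.20 | 5000 | 11 619 | 90% |
| 0.25 | 10 000 | 16 771 | 61% |
| 0.30 | 15 000 | 22 249 | 39% |

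Under these same SDs, power at ΔQ = 0.15 would be above 99%. The range in this table therefore does not start from a true 80%.

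**The case against.** The strongest reply is that 0.04 is conditional. The article does not say that 0.15 comes from MACE. QALYs are built from EQ-5D scores, so quality of life outside MACE counts, and section 2.3 lists other harms such as heart failure, infection and renal failure. The 11% and 15% carry no time point, while the primary clinical outcome is at 30 days, so the one-year difference need not be 4 points. All of this stands, and the conclusion is worded accordingly. It does not rescue 0.15. No non-MACE effect is stated, and one would have to add at least 0.11 QALY per patient on average. Section 2.7.1 itself says that neither strategy has established clinical superiority.

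Second, the claim did not set the sample size, and cost-utility at 1 year is a secondary endpoint, analysed without a stated hypothesis test. That is right, and it limits the consequences. The 80% is still published as a design property in the Abstract.

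Three stronger readings are tempting, and the documents do not support them.
- *The formula does not match the sample size.* The two-sided S of €38 100 implies a QALY SD of about 0.61–0.75 for cost SDs of €20 000 down to €5000, which looks very large for one year. But the SDs used are not shown, and a condensed article may leave them to the full protocol. No mismatch can be computed.
- *The economic power is not real, or is certainly below 80%.* With small enough SDs, power at 0.04 reaches 90%.
- *Power is as low as 6%.* That two-sided figure takes the restrictive strategy as €1000 dearer, against the stated hypothesis.

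Nor is planning a health gain within a noninferiority trial a contradiction: the plan expects 11% versus 15% and allows sequential superiority testing.

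**Conclusion.** The point holds as one of an unsupported planning assumption. The QALY difference behind the 80% is at least 3.75 times what the planned event rates can deliver over the QALY horizon. This assumes that the gain runs through MACE, that the 4-point difference applies over the year, and that utility lies between 0 and 1.

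The size of the effect on power is not established. For the restrictive arm €1000 cheaper and 315 per arm, power at the 0.04 ceiling is 17% two-sided (22% one-sided) if the SD is the one that makes the stated 80% exact. It is 39–90% two-sided under the assumed QALY SD of 0.20–0.30 and cost SD of €5000–15 000. The 0.04 is itself a best case, so a realistic QALY difference would give less. The clinical sample size is untouched by this point.

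**What to change.** In section 2.7.1, replace 0.15 with a QALY difference consistent with 11% versus 15%, or state and justify the non-MACE source of the remainder. Recompute the economic power at 315 per arm with the SDs actually used and the restrictive arm €1000 cheaper, stating the SDs, the sign and the sidedness. Put the resulting figure, with its QALY assumption, in section 2.7.1 and the Abstract in place of 80%.

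If no defensible QALY difference can be given, withdraw the 80% economic power claim in both places and present the cost-utility analysis as estimation.

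The cost is one recalculation and two wording changes. No extra patients are needed. The downside is a stated power that is probably less favourable.

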#### Statistical analyses

2.7.2

Analyses will be performed in both the ITT and PP cohorts. The ITT population is defined as all randomized patients who have signed an informed consent form. In case of consent withdrawal, only data collected before withdrawal will be used. All patients will be analyzed in their randomized arm regardless of the strategy used during the trial. The PP population is defined as all patients randomized and treated without major protocol violations or deviations. Predefined major protocol violations/deviations are: (1) violation of the selection criteria; (2) receipt of the alternative transfusion strategy (apart from in the situations listed below); (3) missing data for the primary efficacy outcomes; (4) inclusion in another interventional study; and (5) major protocol deviation identified during a blinded data review before database lock. Crossover from the restrictive to the liberal strategy will be allowed, and thus not considered a major protocol deviation (so these patients will be included in the PP analysis), in the following documented cases: massive overt active bleeding, presumed important fall in hemoglobin level and no time to wait for hemoglobin testing, or shock occurring after randomization. All statistical analyses will be performed using SAS 9.4 software.

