### Study outcomes

2.3

The primary outcome is the incremental cost‐effectiveness ratio (ICER) at 30 days, using major adverse cardiovascular events (MACE) (composite of all‐cause death, nonfatal stroke, nonfatal recurrent myocardial infarction, or emergency revascularization prompted by ischemia) as the effectiveness criterion. The primary and various secondary outcomes are listed in Table 2.

**TABLE 2 clc23453-tbl-0002:** Outcomes of the REALITY trial

Outcomes	Details
Primary clinical effectiveness composite outcome	
Clinical noninferiority at 30 d	MACE^a^ at 30 days
Primary endpoint	
ICER at 30 d	ICER at 30 days, using the 30 day composite endpoint of MACE^a^ as the effectiveness criterion
Secondary endpoints	
Exploratory outcomes at 30 d	All the components^a^ of the composite clinical outcome will be analyzed separately
Component ICERs at 30 d	ICERs for each individual component of the primary endpoint will be estimated separately
Clinical noninferiority at 1 y	MACE^a^ at 1 y All the components^a^ of this composite clinical outcome will also be analyzed separately as secondary endpoints
ICER at 1 y	ICER at 1 year, using the 1 y composite endpoint of MACE^a^ as the effectiveness criterion
ICUR at 1 y	ICUR at 1 year using QALY at 1 y

Abbreviations: ICER, incremental cost‐effectiveness ratio; ICUR, incremental cost‐utility ratio; MACE, major adverse cardiovascular events.

^a^ All‐cause death, nonfatal stroke, nonfatal recurrent myocardial infarction, or emergency revascularization prompted by ischemia. All components of the composite outcome will also be analyzed separately.

All clinical outcomes (deaths, including cause of death, AMIs, strokes, ischemia‐driven emergency revascularizations, and heart failures) will be reviewed and adjudicated by a CEC. The CEC will be given all relevant clinical and biochemical information and will be blinded to the randomization assignment. In addition, AMIs will be categorized by the CEC according to the Third Universal Definition.^18^ Each triggered event will be reviewed by two CEC members. In case of discrepancy between the two adjudicators, an ad hoc committee with at least three CEC members will reach a final decision based on consensus.

Safety outcomes of special interest, which will be monitored during the index hospitalization, include hemolysis, infections, multiorgan system dysfunction, acute lung injury, acute heart failure, acute renal failure, and severe allergic reactions.

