**FIGURE 1 clc23453-fig-0001:**
[figure not shown]
REALITY trial flow chart. AMI, acute myocardial infarction; RBC, red blood cell

The strategies should be maintained until discharge from hospital or for 30 days, whichever comes first. Special steps are being taken to ensure adherence to the strategy assigned by randomization (particularly if patients are moved to another hospital department): patients receive colored bracelets delineating the transfusion strategy, colored reminder stickers are included in the patients' files, and posters are displayed in the intensive care units. Of note, all medications are left to the discretion of the treating physician and are not dictated by the study protocol.

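### The per-protocol rule has no cut-off at the first MACE, so a restrictive-arm patient transfused because of a primary event can be dropped from PP together with that event

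*Protocol article*

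**What the plan says.** Section 2.7.2 (Statistical analyses) defines the set: "The PP population is defined as all patients randomized and treated without major protocol violations or deviations". Item 2 of its list of major deviations is "receipt of the alternative transfusion strategy (apart from in the situations listed below"). The excused situations are "massive overt active bleeding, presumed important fall in hemoglobin level and no time to wait for hemoglobin testing, or shock occurring after randomization", and they cover one direction only: "Crossover from the restrictive to the liberal strategy will be allowed, and thus not considered a major protocol deviation". The section says these excused patients stay in the PP analysis. Item 5 lets a blinded review before database lock identify further major deviations. For ITT, "All patients will be analyzed in their randomized arm regardless of the strategy used during the trial".

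Section 2.5 sets the trigger at hemoglobin 8 g/dL or below in the restrictive arm and 10 g/dL or below in the liberal arm. The text under Figure 1 gives the duration: "The strategies should be maintained until discharge from hospital or for 30 days, whichever comes first". The clinical outcome is counted over the same month (Table 2: "using the 30 day composite endpoint of MACE"). Section 2.7.5 requires the upper confidence limit for the relative risk to lie below 1.25 "in both the PP and ITT populations".

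**The concern.** In a noninferiority trial, PP is there to expose a difference that crossover has blurred in ITT. It can do that only if leaving PP is not itself a consequence of the outcome. Here the assigned strategy and the endpoint run over overlapping time, and the deviation rule does not stop at the first event. Recurrent infarction, stroke and emergency revascularization are all MACE components, and none is an excused situation. A transfusion prompted by one of them, at a hemoglobin between the two triggers, is a deviation in the restrictive arm and ordinary treatment in the liberal arm. This route therefore removes events from the restrictive arm only. If it is used often enough, PP looks more favorable to the restrictive strategy than the randomized comparison does, and it no longer acts as an independent check.

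**Working it through.** **1. Can the exclusion follow the event?**
- The strategy applies to discharge or day 30, and MACE is counted to day 30. A patient who has a nonfatal event in hospital is still under the strategy afterwards.
- Item 2 names no time point relative to MACE.
- At hemoglobin above 8 and up to 10 g/dL, transfusion is off-strategy in the restrictive arm and on-strategy in the liberal arm.
- The three excused situations do not include the nonfatal MACE components.
- The blinded review is described as identifying deviations. Nothing says it can reinstate a patient excluded under item 2.

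So the rule as written can remove a restrictive-arm patient because of the primary event.

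**2. The plan's own figures (section 2.7.1).** Inputs are 11% against 15%, margin RR 1.25 (0.25 × 15% = 3.75 points), one-sided 0.025 and 80% power. On the risk-difference scale, n = (0.11×0.89 + 0.15×0.85) × (1.960 + 0.842)² / (0.0375 + 0.04)² = 0.2254 × 7.849 / 0.006006 ≈ 295 per group, close to the stated 300. The 5% allowance gives 300/0.95 ≈ 316, against 315 stated. The point below does not depend on how that sample size was obtained. It uses 315 per arm, and the allowance of about 16 patients per arm for all types of violation.

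**3. Effect on PP at the margin.** Take a liberal risk of 15% and a restrictive risk of 18.75%, so the true RR is 1.25 with about 59 and 47 events. Let f be the share of restrictive-arm MACE patients dropped after their event. **The documents give no value for f; the values below are assumptions, and the liberal arm is assumed to lose no one.**

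- PP restrictive risk: p′ = 0.1875(1 − f) / (1 − 0.1875f)
- PP restrictive size: n′ = 315(1 − 0.1875f)
- SE² = (1 − p′)/(n′p′) + 0.85/(315 × 0.15)
- P(PP passes) = Φ[(ln 1.25 − ln RR′)/SE − 1.96]

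For f = 10%: p′ = 0.16875/0.98125 = 0.1720; n′ = 309.1; RR′ = 0.1720/0.15 = 1.146; SE² = 0.01558 + 0.01799, so SE = 0.183; (0.2231 − 0.1367)/0.183 − 1.96 = −1.49; probability 0.068.

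| f (assumed) | Patients dropped | PP RR | PP-alone false pass |
|---|---|---|---|
| 0 | 0 | 1.25 | 2.5% |
| 5% | about 3 | 1.20 | 4.2% |
| 10% | about 6 | 1.15 | 6.8% |
| 20% | about 12 | 1.04 | 16.3% |

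A binomial simulation of 315 per arm gave the same results to within sampling error (4.2%, 6.9%, 16.2%).

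**4. Other directions.** In the same simulation, losing 20% of MACE patients from both arms gives a PP RR of about 1.26 and a PP false pass rate of 2.3%. Losing 20% from the liberal arm only gives 1.52 and about 0.1%.

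**5. The joint rule.** Requiring ITT as well keeps the joint false-pass rate at about 2.5% in every row of the table, because ITT keeps the dropped events.

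**6. When ITT is itself diluted (assumption).** Suppose 20% of restrictive-arm patients cross over before any event, then carry the 15% liberal risk, and are excluded from PP. ITT RR is 0.8 × 1.25 + 0.2 × 1.00 = 1.20, and ITT alone falsely passes 4.2% of the time. With f = 0 in PP the joint rate is 2.1%. With f = 10% or 20% it is 3.5% or 4.1%, so at 20% PP adds almost no protection.

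**The case against.** **The net direction is not fixed by the text.** This stands. Unexcused deviations in the liberal arm are also excluded, and step 4 shows that such losses cancel or reverse the drift. What the text does fix is that one specific loss route exists in the restrictive arm only.

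**The overall error is not inflated.** This stands when ITT is undiluted. A transfusion given after a MACE cannot change an endpoint ITT has already counted. The 4%, 7% and 16% are pass rates for PP alone and must not be read as the trial's false-noninferiority rate. Joint error moves only if separate crossover also dilutes ITT, and then modestly.

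**The route is narrow.** The event must leave time for a transfusion, occur while the strategy applies, be followed by transfusion above the restrictive trigger, and fall outside the bleeding, hemoglobin-fall and shock exceptions. At f = 20% the 12 patients would use three-quarters of the allowance of about 16 per arm. This is fair, and it is why the size is given only as a range.

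**The timing is detail for the full protocol or SAP.** This stands in part: a condensed article need not say how a single off-trigger unit is classified. But the article does state a predefined rule, and its only later step is written as adding deviations.

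**A stronger reading a reader might infer** is that excusing crossover only from restrictive to liberal is what removes restrictive-arm events. The documents do not support it. The excuse keeps patients with massive bleeding or shock, who are probably at high risk, in PP with their events. Its own risk is dilution. Likewise, a liberal-arm patient who dies before transfusion is not clearly a recipient of the other strategy, and excluding such patients would raise the relative risk, away from noninferiority.

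**Conclusion.** The point holds in limited form. The PP rule conditions on an act after randomization with no cut-off at the first MACE, and one resulting loss route operates in the restrictive arm alone. PP is therefore a weaker independent check than the two-population rule intends. The size is unknown. The figures of about 1.20, 1.15 and 1.04 for the PP relative risk rest on assumed shares of 5%, 10% and 20%, no liberal-arm loss and a true relative risk of 1.25. The documents do not support a claim that PP is bound to drift toward noninferiority, or that the trial's overall error exceeds its nominal level through this route alone. The change is worth making because it is nearly free.

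**What to change.** In the PP definition:
- Count departures from the assigned strategy as major deviations only if they occur before the first MACE or, where there is none, up to discharge or day 30. With no events dropped after the fact (f = 0), the PP relative risk at the margin stays at 1.25 and PP alone falsely passes about 2.5% of the time.
- State how the deviation rule classifies patients in each arm, including liberal-arm patients who have an event or die before any transfusion.
- Report PP exclusions by arm and by MACE status.

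The list of permitted crossovers is a treatment rule and should not be extended for this purpose; only membership of the analysis set changes. The cost is a few sentences and a comparison of event and transfusion dates before database lock. No new data are needed if both are dated.
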